#### Data Collection and Monitoring

Screeners will collect data on baseline characteristics when patients are recruited. Assessors will complete records of the assessment of treatment effects, neck physiological function, AEs, and safety evaluations. Next, two data administrators, who are not part of the research team and blinded to group allocation, will independently receive the data outcomes and enter them into a Micrsoft Excel database.

#### Statistical Analysis

The intention-to-treat principle will be followed in the primary data analysis with IBM SPSS Statistics for Windows version 27.0 software by statisticians who are blinded to the group allocation. Baseline characteristics will be expressed with descriptive statistics for the groups as the mean (SD). The Kolmogorov-Smirnov test with Lilliefors correction will be performed to analyze all quantitative variables to determine whether they follow a normal distribution. Parametric statistics (Tukey test) or nonparametric statistics (Wilcoxon rank-sum test) will be used for the within- and between-group analyses in accordance with the results of homogeneity and normality analyses. When initial homogeneity and normality of data distribution are found, repeated measures ANOVA and ANOVA with Bonferroni post hoc statistics will be used for within- and between-group analysis. The Friedman test and the Kruskal-Wallis test will be performed when initial homogeneity but not normality of data distribution is found. If initial homogeneity is not found, a linear mixed model will be adjusted for the baseline value. AEs in each group will be documented as percentages for safety assessments using the chi-square test or the Fisher exact test. Statistical significance is defined as *P*<.05, and 95% CIs will be reported.

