**Methods:**

The parallel, double-blind, three-arm clinical randomized controlled trial (RCT) is being conducted at the Beijing University of Chinese Medicine and its affiliated hospitals. Patients will be recruited and randomly assigned to a PNF group, a tuina group, and a combined (PNF+tuina) group in a 1:1:1 ratio. The PNF intervention (PNF stretching and PNF plyometrics) will last for 30 minutes each session. Tuina therapy will also last for 30 minutes each session. The combined group will receive 30 minutes of PNF, followed by 30 minutes of tuina therapy. Participants will receive 4 weeks of treatment, thrice a week, for a total of 12 treatments. Visual Analogue Scale (VAS) and Neck Disability Index (NDI) scores will be used as primary outcome measures. Cervical active joint mobility measured with the MicroFET3 Portable Muscle Strength Test and Joint Mobility Meter and muscle physical properties tested with the Myoton Muscle Tester will be used as secondary outcome measures. Data will be analyzed at baseline, at the end of the intervention, and during the 4 weeks of follow-up using repeated measures ANOVA. The significance level will be 5%.

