The primary outcome measures of this trial are the VAS and NDI scores. The secondary outcome measures are cervical active joint mobility and muscle physical properties. The three groups will be tested before the intervention (baseline), at the fourth week of the intervention, and at the follow-up visit 4 weeks after the end of the intervention. The study design is illustrated in the flowchart in Figure 1.

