#### Sample Size Calculation

The sample size was calculated using Granmo calculator v.7.12, based on a three-arm parallel-group design and ANOVA for means (SDs). The primary assumption was that the minimum clinically important difference (MCID) according to the VAS score is 13.5% (0.135). This value was derived from a previous NCNP study [27] and represents the minimum pain reduction considered meaningful by patients and clinicians.

The statistical parameters are as follows: alpha risk (type I error): 5% (two-sided); beta risk (type II error): 10% (power=90%); SD of mean VAS scores: estimated as 12% (0.12) based on a pilot study ([name], unpublished data, 2022).

The initial sample size was calculated as 45 participants (n=15, 33.3%, per group) to detect the specified MCID under ideal conditions (no dropouts). To make adjustments for follow-up losses, we anticipated an 8% dropout rate (based on similar rehabilitation trials [8]), so the final sample size was increased to 69 participants (n=23, 33.3%, per group) to ensure at least 20 evaluable patients per group after attrition.

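### The Statistical Analysis section names two sets of tests for the same comparisons without saying how they relate, and the first set puts an independent-samples test on paired within-group data

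*Protocol article*

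**What the plan says.** All of the conflicting text is in one paragraph of the protocol article, Statistical Analysis.

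- **First rule:** "Parametric statistics (Tukey test) or nonparametric statistics (Wilcoxon rank-sum test) will be used for the within- and between-group analyses", with the choice made "in accordance with the results of homogeneity and normality analyses".
- **Second rule, normal data:** "repeated measures ANOVA and ANOVA with Bonferroni post hoc statistics will be used for within- and between-group analysis".
- **Second rule, non-normal data:** "The Friedman test and the Kruskal-Wallis test will be performed when initial homogeneity but not normality of data distribution is found".
- **No initial homogeneity:** "If initial homogeneity is not found, a linear mixed model will be adjusted for the baseline value". This branch is not in dispute.

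The Abstract (Methods) mentions only the parametric route: data are analysed at baseline, at the end of the intervention and "during the 4 weeks of follow-up using repeated measures ANOVA". Study Design shows that each patient is measured before treatment, "at the fourth week of the intervention, and at the follow-up visit 4 weeks after the end of the intervention". Sample Size Calculation sets "alpha risk (type I error): 5% (two-sided", and Statistical Analysis sets significance at P below .05.

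**The concern.** Both rules cover within- and between-group analysis, and both are triggered by the same normality and homogeneity results. Nothing says that one is the follow-up step of the other, or which one governs. A reader could therefore carry out the same comparison in two ways.

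This matters most when the data are judged non-normal. The introduction's primary hypothesis, that the combination reduces pain and disability more than the monotherapies, has to be settled by comparing pairs of arms. Under the first rule these would be rank-sum tests with no stated correction. Under the second, the named between-group test is the three-arm Kruskal-Wallis test.

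The first rule also has a fault of its own. Within an arm, the baseline, week 4 and follow-up scores come from the same patients. The rank-sum test assumes two independent samples, so it ignores the pairing.

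**Working it through.** The plan gives no error rate for these tests, so there is no figure of its own to reproduce. The check compares what each rule implies.

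**Inputs from the protocol article**
- Three arms allocated 1:1:1, so three arm pairs. 23 per arm randomized and at least 20 evaluable (Sample Size Calculation).
- Alpha 5%, two-sided.
- VAS recorded as a whole number from 0 to 10.
- MCID 0.135 and SD 0.12. Read as shares of a 0-10 scale: 0.135 × 10 = 1.35 points and 0.12 × 10 = 1.2 points.

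**Assumptions, not in the documents**
- Between arms: common mean 3.5 and SD 1.5, normal scores rounded to whole numbers and clipped to 0-10.
- Within an arm: baseline mean 5, SD 1.2, before-after correlation 0.3 to 0.7.

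**1. Normal branch.** In 20,000 simulated null trials at 20 and at 23 per arm, the family-wise error is 4.9% to 5.0% with Tukey and 4.2% to 4.3% with Bonferroni. Either choice holds the 5% level.

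**2. Non-normal branch, between arms.** If the three pairs were independent, the chance of at least one false result would be 1 − 0.95³ = 14.3%. Because pairs share arms, the true figure is lower. Results of 20,000 null trials at 20 and at 23 per arm:

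| Procedure and event | Probability |
|---|---|
| Three uncorrected rank-sum tests, any pair significant | about 12% |
| The same, combination versus either monotherapy (two-sided) | about 9% |
| The same, combination better than both | under 1% |
| Kruskal-Wallis alone | about 4.7% |
| Rank-sum pairs only after a significant Kruskal-Wallis | about 4.7% |
| Rank-sum pairs at 0.05/3 | about 4% |

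**3. Is the non-normal branch realistic?** Whole-number scores make it so. With the planned Lilliefors test on rounded normal scores (n = 23, mean 5 assumed), normality is rejected in 83% of samples at SD 1.2, 57% at SD 1.5 and 35% at SD 2.0.

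**4. Within arms.** The rank-sum test takes the variance of the before-after difference as proportional to 2σ². For paired data it is 2σ²(1 − ρ). The actual type I error is therefore roughly P(|Z| > 1.96/√(1 − ρ)). At ρ = 0.5 that is P(|Z| > 2.77), about 0.6%; at ρ = 0.3 it is P(|Z| > 2.34), about 1.9%. Simulation with whole-number scores, n = 23, rank-sum versus signed-rank:

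| ρ | Type I error | Power, 0.6 points | Power, 1.35 points |
|---|---|---|---|
| 0.3 | 2.0% vs 4.5% | 33% vs 45% | 96% vs 98% |
| 0.5 | 1.0% vs 4.8% | 31% vs 58% | 98% vs 99.6% |
| 0.7 | 0.2% vs 5.0% | 28% vs 77% | 99% vs 100% |

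At 20 per arm the gap at 1.35 points stays under 4 percentage points.

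**The case against.** The best defence is that the first sentence is a general statement which the next two make specific, or that it names the pairwise follow-ups. The section says that Kruskal-Wallis will be performed in the non-normal branch, so skipping it is not permitted. Read as gated follow-up, the rank-sum pairs bring the error back to about 4.7%. The Abstract and the ANOVA-based sample size also make the intended parametric lead analysis identifiable. This is a fair reading and it limits the harm, but the section does not state it. It would leave Tukey and Bonferroni both named for the normal branch, and it cannot make a rank-sum test suit paired data.

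Several stronger inferences are tempting and not supported:

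- **That 12% is the false-success rate for the primary hypothesis.** It counts any of the three pairs, including PNF versus tuina. If success means that the combination beats both monotherapies, the rate is under 1% even uncorrected.
- **That the within-group misuse creates false positives.** It is conservative. It also concerns change within an arm, which does not settle the between-arm hypothesis, and the section names suitable repeated-measures methods elsewhere.
- **That the Tukey test is equally wrong within groups.** The text says only Tukey, and Tukey comparisons can use a repeated-measures error term.
- **That the lack of a pairwise step after Kruskal-Wallis is a defect in itself.** An article may leave that to an analysis plan that is not shown. The point here is the two conflicting rules that are printed.

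**Conclusion.** The point holds as a fault in what is written: two test rules for the same comparisons on the same trigger, with no stated relation, and one test that does not fit paired data. It should be fixed, but it does not by itself undermine the trial.

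Its size depends on the branch. With normal data the duplication is harmless. With non-normal data, the chance of some false pairwise difference is about 12% if the rank-sum tests stand alone and uncorrected, against about 5% or less if they are gated by Kruskal-Wallis or corrected. Within arms the cost is power for small changes only, and almost none at 1.35 points.

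The between-arm rates vary little between 20 and 23 patients per arm. The within-arm figures rest on the assumed correlation and on reading the plan's percentages as shares of a 0-10 scale.

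**What to change.** In Statistical Analysis:

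1. Delete the sentence that assigns Tukey or Wilcoxon rank-sum.
2. Normal branch: keep repeated measures ANOVA and ANOVA with Bonferroni.
3. Non-normal branch, between arms: Kruskal-Wallis, followed by pairwise rank-sum tests with Bonferroni or Holm correction.
4. Non-normal branch, within arms: Friedman, followed by Wilcoxon signed-rank tests.

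Make the change before the final analysis, which the Results section projects for October 2025. The Discussion already gives VAS reductions by arm from an interim analysis and calls the combination's reduction significantly greater. The change therefore cannot be presented as made before any by-arm result was seen. Date it and record that those interim results were already reported.

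No extra data or patients are needed. The cost is a short rewrite, and pairwise tests that are slightly less favourable than uncorrected ones.

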The aim of this study is to compare the therapeutic effects of tuina, PNF, and their combination in the treatment of NCNP and whether the combination therapy of PNF and tuina has superior efficacy compared to either therapy alone in order to provide more clinical evidence for the treatment of NCNP. Against this backdrop, this study aims to address three critical research questions:

Does the PNF technique demonstrate superior efficacy compared to tuina in reducing pain and improving functional disability?Does the combination of PNF and tuina yield better outcomes than either monotherapy alone?Are there significant differences in cervical joint mobility and muscle physical properties (eg, stiffness, elasticity) across the three treatment groups?

The specific objectives are to (1) compare the short-term (end of intervention) and long-term (4-week follow-up) efficacy of PNF, tuina, and their combination in reducing pain (VAS score) and functional disability (NDI); (2) evaluate their effects on cervical active joint mobility and muscle physical properties; and (3) assess the safety and tolerability of all interventions. Guided by these objectives, the primary hypothesis is that the PNF-tuina combination will achieve greater reductions in pain and disability than monotherapies, while the secondary hypothesis posits that PNF will outperform tuina in improving cervical biomechanics. All interventions are hypothesized to be safe, with low rates of adverse events (AEs).

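### Baseline enters the repeated measures ANOVA as an outcome visit and no contrast is named for the hypothesised reductions; if the visit-averaged group factor is used, the effect is diluted by a third

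*Protocol article*

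**What the plan says.** - **Hypothesis (Introduction):** "the primary hypothesis is that the PNF-tuina combination will achieve greater reductions in pain and disability than monotherapies". The first specific objective asks the question at two times, the end of intervention and the 4-week follow-up.
- **Visits (Study Design):** "The three groups will be tested before the intervention (baseline), at the fourth week of the intervention, and at the follow-up visit 4 weeks after" (counted from when treatment stops).
- **Model (Abstract, Methods):** "Data will be analyzed at baseline, at the end of the intervention, and during the 4 weeks of follow-up using repeated measures ANOVA". Baseline is therefore a level of the outcome.
- **Between-group method (Statistical Analysis):** when homogeneity and normality are found, "repeated measures ANOVA and ANOVA with Bonferroni post hoc statistics will be used for within- and between-group analysis". No group-by-time term, change score or visit-specific contrast is named.
- **Baseline adjustment (Statistical Analysis):** conditional only. "If initial homogeneity is not found, a linear mixed model will be adjusted for the baseline value".
- **Planning values (Sample Size Calculation):** the calculation is "based on a three-arm parallel-group design and ANOVA for means (SDs"), with "the minimum clinically important difference (MCID) according to the VAS score is 13.5% (0.135") and "SD of mean VAS scores: estimated as 12% (0.12) based on a pilot study".

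**The concern.** A repeated measures ANOVA with three arms and three visits gives a visit effect, a group effect and their interaction. The group effect, and post hoc pairs computed on it, compare each arm's mean over all the visits entered. Its null hypothesis is equal three-visit averages. Randomisation makes the expected baseline equal across arms, so one of the three values averaged carries no treatment effect.

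The hypothesis is about reductions, which are tested by the interaction or by a contrast at a given post-treatment visit. By leaving the deciding term open, the plan allows tests with different null hypotheses and quite different power on the same data. A reading through the group factor could miss a benefit of the size the trial was planned for. It also could not give the separate end-of-intervention and follow-up answers that the first objective asks for.

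**Working it through.** **Inputs from the documents.** Difference d = 0.135 and SD = 0.12 (1.35 and 1.2 points on the 0 to 10 VAS), two-sided 5%, 23 per arm planned, at least 20 evaluable per arm (Sample Size Calculation). Three visits (Study Design).

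**Assumptions.** The same correlation r between any two visits; the documents give none, so a range is shown. The combined arm is better by d at both post-treatment visits, and the two monotherapies are equal. Bonferroni over three pairs, so α = 0.05/3.

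**The plan's own figure.** The initial 15 per group at 90% power does not reproduce with a two-sided 5% test: power at 15 is 84% (two-group t test) or 88% (ANOVA F test with means 0, 0, d), and 17 to 18 per group are needed. That is a separate matter and is not used here. The power figures below start from d, SD and the planned 23.

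**Dilution.** Difference in three-visit means = (0 + d + d)/3 = 2 × 0.135/3 = 0.090.

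**SD of a patient's three-visit mean.** SD × √((1 + 2r)/3). At r = 0.5 this is 0.12 × √(2/3) = 0.098.

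**Pairwise power.** Noncentral t with 3 × (23 − 1) = 66 df, critical value 2.457, and noncentrality = difference/(SD × √(2/23)).
- Week-4 ANOVA: 0.135/(0.12 × 0.2949) = 3.82, power 91%, whatever r is.
- Group factor at r = 0.5: 0.090/(0.098 × 0.2949) = 3.11, power 74%.
- Change from baseline at week 4: SD × √(2(1 − r)).
- Week-4 ANCOVA with baseline as covariate: residual SD = SD × √(1 − r²), 65 df.

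| r | SD of three-visit mean | Group factor | Week-4 ANOVA | Week-4 change | Week-4 ANCOVA |
|---|---|---|---|---|---|
| 0.3 | 0.0876 | 84% | 91% | 78% | 94% |
| 0.5 | 0.0980 | 74% | 91% | 91% | 97% |
| 0.7 | 0.1073 | 65% | 91% | 99% | >99% |
| 0.8 | 0.1117 | 61% | 91% | >99% | >99% |

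**With 20 evaluable per arm.** Group factor 78%, 67%, 58%, 54%; week-4 ANOVA 86%; ANCOVA 89%, 95%, 99%, >99%.

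**Size needed for 90% pairwise power on the group factor.** 27, 34, 40 and 43 per arm, against 23 planned.

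**Omnibus tests at 23 per arm.** The loss is smaller: group factor 95%, 89%, 83%, 79%, against 98% for a week-4 ANOVA. The group-by-time term gives 94%, 99%, >99%, >99%.

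**The case against.** The strongest reply is that the plan never says the group main effect decides.

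- The sentence lists two methods for two purposes. It can be read as repeated measures ANOVA within groups and one-way ANOVA between groups. The non-normal counterparts support this: Friedman is a within-patient test with no group factor, and Kruskal-Wallis is a one-way group comparison.
- The sample size rests on a plain ANOVA of means, and the Discussion compares the arms' VAS reductions at 4 weeks. Both point to comparison at a visit.
- If one three-visit model is fitted, it also yields the group-by-time term, which does test different reductions.
- A condensed article may leave the choice of term to the analysis plan.

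Most of this stands. A reader might infer that the plan tests the wrong null hypothesis and that power falls sharply as a matter of course. The documents do not support that; the loss is conditional on one of several readings. A reader might also assume that the effect fades by follow-up, which would dilute the average further, but the documents give no fading figure. The size of the loss also depends on an unstated correlation.

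The reply does not remove the mismatch in what the article itself fixes. It puts baseline among the outcome visits, assigns the repeated measures model to within- and between-group analysis together, and withholds baseline adjustment in its default path, while its hypothesis is about reductions.

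**Conclusion.** The point holds as a conditional one. The plan names no contrast for its own primary hypothesis, and one permitted reading of its model dilutes a fully sustained effect by one third. On that reading pairwise power at 23 per arm is 61% to 84% for r from 0.8 down to 0.3. That is 7 to 30 percentage points below a week-4 ANOVA, and further below a baseline-adjusted comparison. On the other readings there is no such dilution. The figures rest on the plan's difference and SD, equal correlation between visits, equal monotherapies and an effect held to follow-up. Whichever reading was intended, a baseline-adjusted contrast at each visit is at least as powerful as the other pairwise tests compared here and answers the first objective directly. This is therefore a free improvement and not proof of a wrong test.

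**What to change.** State in the Statistical Analysis section that:

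1. The between-group efficacy results are the pairwise group contrasts at week 4 and, separately, at the 4-week follow-up, each with a 95% CI.
2. They come from an ANCOVA at each visit, or a linear mixed model with group, visit and group-by-visit terms, with only the two post-treatment visits as outcomes.
3. Baseline is a covariate whatever the homogeneity test shows. With baseline as a covariate, the group contrast in the score equals the group contrast in the reduction, so it tests the stated hypothesis.
4. The group factor averaged over visits, and post hoc tests on it, are not used for efficacy.

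Unadjusted change scores are not a good substitute: at r = 0.3 they give 78% pairwise power against 91% for the week-4 ANOVA. Align the Abstract with the new text, and record the change before the final analysis.

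The cost is a change of wording and model. The plan already names a baseline-adjusted linear mixed model for one branch. No patients, visits or measurements are added.

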#### Outcome Measurements

Two self-report tools and two detectors will be used to measure the outcomes. The VAS and NDI scores will be used as the primary outcome measures. Cervical active joint mobility measured with the MicroFET3 Portable Muscle Strength Test and Joint Mobility Meter and muscle physical properties tested with the Myoton Muscle Tester will be used as secondary outcome measures. Pain, cervical active joint mobility, cervical spine dysfunction, and muscle physical property measurements will be performed during the first week (preintervention) and after 4 weeks’ treatment.

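### The primary hypothesis rests on two contrasts that the analysis reaches only as post hoc pairs; the stated 90% power is for an omnibus VAS test, and no success rule covers VAS, NDI and the two visits

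*Protocol article*

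**What the plan says.** All references are to the protocol article.

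- **Hypothesis (Introduction).** "the primary hypothesis is that the PNF-tuina combination will achieve greater reductions in pain and disability than monotherapies". This needs combined versus PNF and combined versus tuina.
- **Other aims (Introduction).** The first listed research question concerns the third pair: "Does the PNF technique demonstrate superior efficacy compared to tuina in reducing pain and improving functional disability". The first objective is to "compare the short-term (end of intervention) and long-term (4-week follow-up) efficacy of PNF, tuina, and their combination".
- **Primary outcomes (Study Design).** "The primary outcome measures of this trial are the VAS and NDI scores". The same paragraph places all three groups' tests at baseline, week 4 and a visit 4 weeks after treatment ends.
- **Visits elsewhere.** Outcome Measurements lists only two occasions for pain, dysfunction, mobility and muscle properties: "muscle physical property measurements will be performed during the first week (preintervention) and after 4 weeks". Safety Evaluation says efficacy will be evaluated over the 4-week follow-up, but the only contact it describes is by phone at weeks 4 and 8.
- **Test (Statistical Analysis).** When data are homogeneous and normal, "repeated measures ANOVA and ANOVA with Bonferroni post hoc statistics will be used for within- and between-group analysis". Other branches name Tukey, Wilcoxon rank-sum, Friedman, Kruskal-Wallis or a linear mixed model. One threshold is given: "Statistical significance is defined as *P*<.05, and 95% CIs will be reported".
- **Sample Size Calculation.** A three-arm ANOVA on VAS alone, with "alpha risk (type I error): 5% (two-sided"), 90% power, difference 0.135 and SD 0.12. This gives 15 per group, raised to 23 so that at least 20 remain evaluable.

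**The concern.** Hypothesis, test and sample size should concern the same comparison, and here they do not. The hypothesis is about the combination against each monotherapy. The sample size is for any difference among three arms. The analysis reaches the two relevant contrasts only as members of a set of three post hoc pairs.

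Two consequences follow, under different readings of success. If success means beating both monotherapies, the stated 90% power does not carry over to that claim. If success means any significant pair on either primary outcome, the chance of a false positive exceeds 5%, because the correction acts only within a set of three pairs. The article does not say which reading applies, so a reader of the results could not tell whether a given pattern confirms the hypothesis.

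**Working it through.** **1. Inputs.** Difference 0.135, SD 0.12, two-sided alpha .05, power 90%, 15 per group before attrition, 23 after, 8% dropout, at least 20 evaluable (all Sample Size Calculation). Standardised difference d = 0.135/0.12 = 1.125. Evaluable after dropout: 23 × 0.92 = 21.2, so 21.

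**2. Reproducing the stated 15 per group.** Take an omnibus test on 2 degrees of freedom, with one arm differing from two equal arms. For 90% power the large-sample noncentrality is 12.654. The sum of squared deviations of the arm means, in SD units, is 1.125² × 2/3 = 0.84375. Then n = 12.654/0.84375 = 14.997, that is 15 per group. The exact F test has 87.7% power at 15 and needs 17. A two-group comparison at .05 also needs 17. So the stated figure is an omnibus ANOVA figure.

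**3. Power for the primary hypothesis on VAS.** Assume the combination is better than both monotherapies by 0.135 and the monotherapies are equal. Each contrast uses t = difference/(pooled SD × √(2/n)) on 3n − 3 degrees of freedom. Its noncentrality is 1.125 × √(n/2), and the two contrasts correlate at 0.5 because they share an arm. Success requires both to be significant in favour of the combination (400,000 simulated trials):

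| Evaluable per arm | Noncentrality | Both, three-pair Bonferroni (.05/3) | Both, each at .05 | Loss (points) |
|---|---|---|---|---|
| 20 | 3.56 | 77.3% | 89.3% | 12.0 |
| 21 | 3.65 | 80.0% | 91.0% | 11.0 |
| 23 | 3.81 | 84.9% | 93.6% | 8.7 |

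At 20 per arm the omnibus F test has 95.6% power. Requiring it to be significant first leaves the Bonferroni figure at 77.3%.

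**4. Why requiring both needs no alpha split.** If the combination is not better than at least one monotherapy, a joint claim requires a false rejection of that contrast. That has probability at most .05 two-sided, hence at most .025 in favour of the combination.

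**5. The loss under other readings.** For a single contrast, .05/3 against .05: 93.7 − 85.9 = 7.8 points at 20 per arm and 96.4 − 91.0 = 5.4 at 23. For both contrasts, three-pair against two-pair Bonferroni: 82.2 − 77.3 = 4.9 points at 20 and 88.6 − 84.9 = 3.7 at 23.

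**6. Family error if any significant pair counts.** Global null, 21 per arm, Bonferroni within each outcome-by-visit set of three. The article gives no correlations, so 0.3 to 0.7 between outcomes and 0.5 to 0.7 between visits are assumed.

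- Two outcomes, one visit (6 pairs): about 7% to 8%.
- Two outcomes, both visits tested separately (2 × 2 × 3 = 12 pairs): about 12% to 15%, and about 16% if all four sets were independent.
- Of those 12 pairs, 8 compare the combination with a monotherapy. A false claim in either direction among these occurs in about 9% to 11% of trials. A false claim favouring the combination occurs in about 4% to 6%, against a nominal 2.5%.

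**The case against.** The strongest counter-case has five parts.

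- **The hypothesis is tested.** A reader might infer that the planned analysis misses the primary hypothesis altogether. It does not: the three Bonferroni pairs include both relevant contrasts. The fault is their status as post hoc pairs and the sample size set for a different test.
- **PNF versus tuina is a stated question.** A reader might infer that alpha spent on that pair is simply wasted. It answers the first listed research question, and correcting over all three pairs is conventional. What stands is that the pair lies outside the primary hypothesis and can be secondary.
- **Twelve tests are not prescribed.** Repeated measures ANOVA gives one analysis per outcome across visits. The article never says that pairs are compared separately at each visit, and Bonferroni belongs to one branch only. The 12% to 15% is therefore conditional.
- **The two harms use opposite readings.** Error inflation assumes that any win counts; the power loss assumes that both monotherapies must be beaten. They cannot both apply in full. If pain and disability must both improve, no correction across outcomes is needed. This stands, and it shows that the missing success rule is the root of the problem.
- **Alpha allocation may sit in a separate analysis plan.** That could settle the rule for outcomes and visits. It would not remove the mismatch between hypothesis and sample size, or the disagreement among sections about follow-up measurement, since both are in the article.

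**Conclusion.** The point holds in conditional form. The stated 90% power does not carry over to the primary hypothesis. For beating both monotherapies on VAS at 20 to 23 evaluable per arm, it is about 77% to 85% under three-pair Bonferroni and 89% to 94% with each contrast at .05. The difference of 9 to 12 points belongs to that reading; others give 4 to 8. If any significant pair counts, family error is about 7% to 8% at one visit and 12% to 15% with separate tests at both.

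These figures assume the planned effect against both monotherapies, a common SD of 0.12, normal data and the assumed correlations. They also take the total as 69, as in Randomization and Sample Size Calculation. Study Design gives 102; at 34 per arm, three-pair Bonferroni would give 97.3% for beating both, so the shortfall depends on 69 being the true target.

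The change should be made, but it is not free of risk. The Discussion already reports an interim comparison in which the combination had a larger VAS reduction at 4 weeks (42% against 28% and 31%). Making week-4 VAS the sole deciding endpoint now would look data-driven unless its timing and grounds are disclosed.

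**What to change.** 1. In Statistical Analysis, name combined versus PNF and combined versus tuina as the primary contrasts. Test each at two-sided .05 and claim superiority only if both are significant in favour of the combination.
2. Fix one primary visit and one rule for VAS and NDI. Either require both, in line with the hypothesis, or test in a fixed order with VAS first, on the ground that only VAS was sized.
3. Make the other visit and PNF versus tuina secondary.
4. In Sample Size Calculation, restate power for the chosen rule. Power will be lower if NDI is also required, and the article gives no NDI effect or SD from which to compute it.
5. Date the change and disclose that it follows the interim week-4 VAS comparison.
6. Reconcile Outcome Measurements and Safety Evaluation with the Introduction and Study Design on whether VAS and NDI are measured at the 4-week follow-up.

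The cost is wording and a dated amendment, with no added patients. The price in claims is that a win over only one monotherapy, or at the non-primary visit, is no longer a primary success.
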